#### Control group (CG)

Participants in the CG will receive the standard care package prescribed on hospital discharge, which may vary across study hospitals. Variations in standard care will be investigated through qualitative process evaluation and reported in the results manuscript. In case of adverse physical or psychological health conditions, they will access care through the usual available channels.

#### Intervention group (EMDR)

Participants randomised to the intervention group will receive the standard clinical care package following hospital discharge. Additionally, they will be referred to a participating adult NHS Psychological Therapies service using the established NHS–NHS referral system, identifying them as EMERALD participants. NHS Psychology teams will adhere to this research protocol for treatment. Any deviations from the protocol will be reported to the study team.

EMDR sessions, whether conducted via videoconference or face-to-face, will ideally commence within 4 weeks of referral and will be administered by trained EMDR therapists, who are supervised by a Consultant Clinical Psychologist. EMDR comprises eight phases, providing a structured treatment framework that supports consistency in session effects. The protocolised nature of EMDR facilitates training and replication in controlled studies. With participant and therapist agreement, some sessions will be recorded and assessed using the EMDR Fidelity Rating Scale (EFRS)^30^ to allow granular reporting of the delivered intervention. The EMDR protocol, reported according to the TIDieR (template for intervention description and replication) guidelines, is available in online supplemental file 2. Sessions will last up to 60 min, and therapist-recorded adherence will track the number of sessions offered versus those completed. Participants may receive up to 16 EMDR sessions based on the therapist’s ongoing assessment of need.

10.1136/bmjopen-2023-081969.supp2Supplementary data

### Outcome measures

Primary outcome measures are feasibility and acceptability of trial process, to participants and staff.

Feasibility will be reported using the Consolidated Standards of Reporting Trials (CONSORT) statement as follows:

Recruitment rate part A—we anticipate an average recruitment of 10 patients per month across the three participating sites. This is well above the median recruitment of 0.95 participants recruited per site per month, reported in a review of trials listed in the NIHR journals library (1997–2020).^31^Consent rate—number of patients recruited, expressed as a percentage of patients approached. Based on our previous work, we expect this to be greater than 30%.^28^Adherence will be determined by completion of ≥75% of planned EMDR sessions completed.Retention will be determined by ≥75% of participants completing the study follow-up assessment.

Acceptability will be determined by a qualitative process evaluation using semistructured interviews, and reported according to the Theoretical Framework of Acceptability.^32^ In addition, we will assess fidelity to the EMDR delivery model using the EFRS. This will enable us to account for variability in intervention delivery. Safety will be determined by assignment of causality of serious events. Events attributable to trial procedures will be reviewed by trial management board, study sponsor and the Research Ethics Committee (REC) to determine ongoing feasibility.

In addition to sociodemographic characteristics, and medical history (including ICU admission data), secondary outcome measures will be collected at baseline, 2 months and 12 months posthospital discharge to capture possible clinical outcomes, mediators, moderators and covariates that may be included in the subsequent, definitive effectiveness trial. A detailed description of each of these measures is provided in online supplemental file 3. All data will be stored securely, pseudonymised by study number, on the Qualtrics electronic database. The secondary outcome measures include the following:

10.1136/bmjopen-2023-081969.supp3Supplementary data

Change in PTSD symptom severity using the Impact of Events Scale-Revised (IES-R)^33^Change in categorical diagnosis of PTSD using IES-R.Post-traumatic stress score using Clinician administered PTSD scale for DSM-5 (CAPS-5)^34^Clinical Global Impression-Severity scale (CGI-S).^35^Sensitivity analysis: to determine whether PTSD symptom burden identified by IES-R corresponds with those identified by CAPS-5.Anxiety: Generalised Anxiety Disorder-7 (GAD-7)^36^Depression: Patient Health Questionnaire-9 (PHQ-9)^37^Quality of life EuroQol Five Dimension-Five level scale (EQ5D-5L).^38^Clinical Global Impression of Improvement (CGI-I).^35^

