## Methods: participants, interventions and outcomes

### Design

This is a multicentre, mixed-methods, randomised controlled pilot feasibility study, with a two-part consent process and is reported using the Standard Protocol Items: Recommendations for Interventional Trials (SPIRIT) reporting guidelines^29^ (online supplemental file 1: Reporting checklist for protocol of a clinical trial). Initially, all participants enter part A, which is an observational study, where they complete a series of mental health questionnaires at baseline, 2 months and 12 months posthospital discharge. If a participant shows symptoms of post-traumatic stress at the 2 month mark (scoring≥22 on the Impact Events Scale-Revised (IES-R)), they are invited to consider participating in part B, which is an interventional study of EMDR versus standard care. Those without post-traumatic stress symptoms at 2 months (≤21 on the IES-R) or those who decline participation in part B will be offered continuation of the observation arm. All participants from both part A and part B repeat the study assessments at 12 months posthospital discharge. See figure 1 for the participant timeline.

10.1136/bmjopen-2023-081969.supp1Supplementary data

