### Part A participant recruitment

Recruitment is anticipated to occur between February 2023 and May 2024. Eligibility screening will target consecutive patients discharged from the participating ICUs. Research staff will approach eligible patients on hospital wards or within 2 months following hospital discharge, via a telephone call or email, providing a participant information sheet. Patients will be invited to complete an informed consent form (ICF), accessible electronically through Qualtrics on tablet devices provided by the trial team, via an emailed link or on paper to suit patient preference. This initial consent pertains to their participation in the observational study (part A), involving baseline data collection and psychometric assessments, with a follow-up evaluation at 2 months and 12 months following hospital discharge.

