### Sample size

As this is a feasibility study, an a priori sample size calculation is not applicable. The findings will guide the sample size determination for a potential definitive RCT. Sample sizes of feasibility studies between 24 and 50 have been recommended to provide adequate estimate of SD for sample size calculation.^39 40^

To achieve this, a total of 160 patients will be enrolled in part A to assess feasibility adequately. Based on an expected incidence of 20%–25% post-ICU PTSD, we anticipate that around 40 patients will proceed to the part B RCT with an IES-R PTSD score≥22. The remaining 120 participants will continue in the observation arm, with a 12 month reassessment. Accounting for an estimated 25% mortality or loss to follow-up across all study arms, we anticipate approximately 30 participants completing the RCT and 90 participants completing the observation arm.

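### The recruitment-rate measure and its benchmark describe observational Part A, and the listed feasibility measures include no randomisation rate for the Part B trial

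*Protocol article*

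**What the plan says.** The Outcome measures section lists how feasibility will be reported. The first item reads: "Recruitment rate part A—we anticipate an average recruitment of 10 patients per month across the three participating sites". It continues: "This is well above the median recruitment of 0.95 participants recruited per site per month", a figure "reported in a review of trials listed in the NIHR journals library (1997–2020"). The second item is "Consent rate—number of patients recruited, expressed as a percentage of patients approached", with an expectation above 30%; it does not say whether this means consent to Part A or to Part B. The other two items are adherence to EMDR sessions and retention, each at 75% or more.

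The Design section describes the two stages: "Initially, all participants enter part A, which is an observational study". Participants scoring 22 or more on the IES-R at 2 months are then invited to Part B, the randomised comparison. Part B has its own information sheet and consent, and those who decline may stay under observation.

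For timing, Part A participant recruitment states: "Recruitment is anticipated to occur between February 2023 and May 2024". For numbers, Sample size states that "a total of 160 patients will be enrolled in part A to assess feasibility adequately". It takes 20% to 25% as the expected share with PTSD, anticipates about 40 entering Part B, and cites 24 to 50 as a recommended size for feasibility studies.

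**The concern.** The primary objective is the feasibility and acceptability of EMDR for patients with traumatic stress symptoms, as groundwork for a fully powered RCT. EMDR is offered only in Part B. The step a definitive trial most needs to know about is how many screen-positive patients accept randomisation, and how fast. The stated recruitment rate measures an earlier and easier step: agreeing to complete questionnaires. Setting that rate beside a median from a review of trials invites the reader to conclude that trial recruitment is comfortably feasible, and the comparison cannot show that.

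At stake is what the feasibility report can conclude. Part A could recruit 10 a month with more than 30% consenting, and those few who enter Part B could attend their sessions and complete follow-up. Every listed measure would then be met although too few patients accepted randomisation to support the next trial.

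**Working it through.** **Inputs, all from the protocol article**
- Three sites; 10 patients a month in Part A; benchmark 0.95 per site per month; consent above 30% (Outcome measures).
- Window February 2023 to May 2024: 16 calendar months counted inclusively, 15 counted start to start (Part A participant recruitment).
- 160 in Part A; 20% to 25% above threshold; about 40 in Part B; cited range 24 to 50 (Sample size).

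**Reproducing the plan's figures**
- 10 per month × 16 months = 160, as stated. Fifteen months would give 150, so 16 is the window that fits the plan.
- 160 × 0.25 = 40, as stated. 160 × 0.20 = 32, so the 40 uses the top of the range. It also allows for no refusals and no loss before the 2-month screen.

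**Rates in the benchmark's unit**

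Rate = N / (sites × months). With 3 sites and 16 months there are 48 site-months.
- Part A: 160 / 48 = 3.33 per site per month, and 3.33 / 0.95 ≈ 3.5. The claim holds for Part A after converting the three-site total to a per-site rate.

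| Part B entrants | 15 months (45 site-months) | 16 months (48) | 18 months (54; adds the 2-month screening lag) |
|---|---|---|---|
| 40 (25%) | 0.89 | 0.83 | 0.74 |
| 32 (20%) | 0.71 | 0.67 | 0.59 |

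Every entry is below 0.95.

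**What it would take to reach 0.95**
- Over 48 site-months: 0.95 × 48 = 45.6, so 46 randomised. 45.6 / 160 = 28.5% of Part A, above the planned 20% to 25% even with full uptake.
- With 40 randomised: 40 / (3 × 0.95) = 14.0 months, shorter than the stated window.

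**If the 30% consent expectation were applied to Part B**
- 0.30 × 32 = 9.6 and 0.30 × 40 = 12, so about 10 to 12 randomised, or 0.20 to 0.25 per site per month. Both counts are below the cited 24 to 50.
- Reaching 24 needs uptake of 24 / 40 = 60% at the top of the range, or 24 / 32 = 75% at the bottom.

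The 30% expectation therefore does not safeguard Part B under either reading. Read as Part A consent it does not address randomisation; read as Part B consent it could be met with too few patients.

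**The case against.** The sentence is openly labelled as Part A and is true in the benchmark's own unit, so there is no arithmetic error and nothing is concealed. Part A inflow is a proper feasibility measure, because it is the only route into the RCT. The 0.95 is context: no decision in the protocol depends on exceeding it, and as a median it was missed by about half of the reviewed trials. The article does not say whether the review counted consents, enrolments or randomisations. The protocol gives a planning expectation of about 40 for Part B, the CONSORT diagram will show the count, and the interviews may explain poor uptake.

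All of this stands, and it limits the point. A reader might infer that the RCT is shown to fall short of the norm for trials. The documents do not support that: what the median counted cannot be seen, and 0.83 or 0.89 against 0.95 is a modest gap. A reader might also infer that the protocol would formally declare recruitment feasible on Part A alone. It contains no progression rule, so that goes too far. Nor can it be said that the consent expectation excludes Part B; it is unassigned.

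What the objection does not supply is a listed measure for uptake at the second consent. The figure of 40 stands under Sample size as an expectation, and a flow diagram reports a count without saying what it will be judged against. That the article condenses a fuller protocol does not remove the point, because it rests on what the article states: a rate assigned to Part A, and a comparison drawn from it.

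**Conclusion.** The concern holds as one of measurement and inference. The recruitment rate and its benchmark describe entry to an observational cohort and do not inform recruitment to the RCT. On the plan's own numbers Part B would run at about one fifth to one quarter of the Part A rate (32/160 to 40/160), which is below the quoted median over the stated window.

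These Part B rates assume that all three sites recruit throughout, that every eligible patient accepts, and that none is lost before the 2-month screen. Refusals or early losses would lower them; a share above threshold higher than planned would raise them. The conclusion that a feasibility measure is misplaced depends on none of these assumptions.

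This should be fixed, because it bears on the primary objective. It does not call the design, the sample size or the data collection into question.

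**What to change.** 1. Add two primary feasibility outcomes, each with a 95% confidence interval:
   - participants randomised per site per month, with the site-months defined, judged against the plan's own expectation (40 / 48 = 0.83 if 40 is kept);
   - Part B consent, defined as the number randomised divided by the number with IES-R of 22 or more who were approached.
2. State which consent stage the expectation above 30% refers to.
3. Keep the Part A recruitment rate as a process measure.
4. Delete the claim of being well above the median, or qualify it as a Part A figure and give the expected Part B rate beside it.

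The cost is outcome wording. The counts come from the screening log and the CONSORT diagram, so no new data are needed. The downside is that the benchmark comparison becomes less favourable.

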### Sample size

As this is a feasibility study, an a priori sample size calculation is not applicable. The findings will guide the sample size determination for a potential definitive RCT. Sample sizes of feasibility studies between 24 and 50 have been recommended to provide adequate estimate of SD for sample size calculation.^39 40^

To achieve this, a total of 160 patients will be enrolled in part A to assess feasibility adequately. Based on an expected incidence of 20%–25% post-ICU PTSD, we anticipate that around 40 patients will proceed to the part B RCT with an IES-R PTSD score≥22. The remaining 120 participants will continue in the observation arm, with a 12 month reassessment. Accounting for an estimated 25% mortality or loss to follow-up across all study arms, we anticipate approximately 30 participants completing the RCT and 90 participants completing the observation arm.

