### Two-month posthospital discharge assessment

All participants will be requested to repeat the IES-R, PHQ-9, GAD-7 and EQ-5D-5L. These patient-reported outcome measures can be completed electronically via an emailed link or by using paper versions sent with a prepaid return envelope.

The study team will review the IES-R responses. Participants with a total score≥22, indicative of post-traumatic stress symptoms, will be approached to consider participation in an EMDR versus usual care RCT (part B).

Participants without symptoms (IES-R≤21) or those not interested or unable to participate in the RCT will continue in the observational study, completing the 12 month follow-up assessment.

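### The Sample size section gives best-case figures as the anticipated ones: 40 entering the RCT and 30 completing need the 25% end of the 20–25% range and no refusals of Part B

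*Protocol article*

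**What the plan says.** The Sample size section of the protocol article states that "a total of 160 patients will be enrolled in part A to assess feasibility adequately". It takes the proportion expected to be above threshold as 20% to 25% and concludes: "we anticipate that around 40 patients will proceed to the part B RCT with an IES-R PTSD score≥22". It then says "The remaining 120 participants will continue in the observation arm, with a 12 month reassessment". The last step removes a quarter of every group for death or dropout, with this result: "we anticipate approximately 30 participants completing the RCT and 90 participants completing the observation arm". The rationale offered for these numbers is a recommended range of 24 to 50 for feasibility studies, cited as adequate for estimating an SD.

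Other sections describe how people reach the RCT. Under Design and Part B participant recruitment, a participant scoring 22 or more on the 2-month IES-R is offered Part B, receives a separate information sheet and consent form, and may refuse. The two-month assessment section says that "those not interested or unable to participate in the RCT will continue in the observational study". No expected Part B consent rate is given, and the timing of the 25% loss is not stated.

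**The concern.** The chain from 160 to 40 has a single multiplier, 25%. That is the favourable end of the section's own range, and the chain has no term for refusing Part B, although the article describes that refusal and says where decliners go. The 120 in observation points the same way: it is exactly 160 minus all those above threshold, so it contains no decliners.

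The only justification for the size is an adequate SD, and under Objectives the variance estimates are meant to feed the definitive trial's sample size. Table 1 schedules the CAPS-5 for Part B participants only, so for that measure the observation arm cannot make up a shortfall. A planning figure that holds only in the best case overstates what the RCT can be relied on to supply. It also leaves the study without a stated Part B uptake against which to judge the observed one.

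**Working it through.** **Inputs.** From Sample size: 160 enrolled; 20–25% above threshold; 25% mortality or loss, so 75% retained (Outcome measures uses the same 75% as its retention criterion); target range 24–50. From Design, the two-month assessment and Part B recruitment: a second consent that can be declined, rate not given (call it c).

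**Formula.** Randomised = 160 × prevalence × c. Completing = randomised × 0.75. Observation = 160 − randomised.

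**Reproducing the stated figures.** With prevalence 25% and c = 1: 160 × 0.25 = 40; 160 − 40 = 120; 40 × 0.75 = 30; 120 × 0.75 = 90. All four match. Neither the lower end nor the midpoint of the range reproduces them.

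| Prevalence (c = 1) | Randomised | Completing | Observation | Observation completing |
|---|---|---|---|---|
| 20% | 32 | 24 | 128 | 96 |
| 22.5% | 36 | 27 | 124 | 93 |
| 25% | 40 | 30 | 120 | 90 |

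Taking the counts as binomial with n = 160, the chance of at least 40 above threshold is 0.07 at 20%, 0.25 at 22.5% and 0.53 at 25%. With full consent at 20%, the chance of at least 24 completers (probability 0.20 × 0.75 = 0.15 each) is 0.53.

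**Part B consent needed to reach 24.**

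| Prevalence | For 24 completing | For 24 randomised |
|---|---|---|
| 20% | 24/24 = 100% | 24/32 = 75% |
| 22.5% | 24/27 = 89% | 24/36 = 67% |
| 25% | 24/30 = 80% | 24/40 = 60% |

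**Effect of an assumed consent rate.** These rates are assumptions; the article gives none.

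- At 70%: 160 × 0.20 × 0.7 = 22.4 to 160 × 0.25 × 0.7 = 28 randomised; × 0.75 gives 16.8 to 21 completing. Observation is then 160 − 28 = 132 to 160 − 22.4 = 137.6, not 120.
- At 50%: 16 to 20 randomised, 12 to 15 completing.

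**Loss before the 2-month screen.** Only those who complete the 2-month IES-R can be identified for Part B.

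- If the 25% runs from enrolment, 160 × 0.75 × 0.25 = 30, so the stated 30 is unchanged. The 40 is overstated to the extent that loss precedes the screen.
- If early loss comes on top of the 25%, both fall. With an assumed 10% early loss and full consent: 28.8 to 36 randomised, 21.6 to 27 completing.

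**Effect on the SD.** The 95% limits for a pooled SD, as multiples of the estimate, are √(df/χ²) with df = n − 2. They are 0.79 to 1.35 at n = 30, 0.77 to 1.42 at n = 24, and 0.76 to 1.46 at n = 21.

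**The case against.** The best reply is that nothing is miscalculated. The section says a formal calculation does not apply, hedges its figures as approximate, and belongs to a study whose purpose is to measure recruitment and retention. With full consent, its inputs stay within 24–50 throughout. The cited range is not tied to completers; if it means those randomised, 60–75% consent is enough when there is no loss before the screen. The loss in precision is also gradual: the SD limits at 21 are almost those at 24. Decliners still complete the 12-month IES-R, PHQ-9, GAD-7 and EQ-5D-5L, so some usual-care variance information remains.

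Most of this stands, and it limits the point to a planning statement. It does not rescue the stated figures. Approximate wording does not cover using one end of a quoted range, or leaving out a step that the same article describes. Decliners' questionnaires do not supply the CAPS-5, and decliners may differ from those who accept randomisation.

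A reader might go further and infer that the RCT is expected to fall short of 24–50. The documents do not support that. A shortfall needs a Part B consent rate that they do not give. The consent rate above 30% under Outcome measures is patients recruited over patients approached, which reads as entry to the study. It should not stand in for uptake among people who have already joined, completed questionnaires and screened positive.

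**Conclusion.** The point holds as a misstatement of the anticipated size. The 40 randomised, 120 in observation and 30 completing require 25% prevalence and 100% consent to Part B; the 40 also requires no loss before the 2-month screen. On the plan's own range with full consent, the figures are 32–40 randomised and 24–30 completing.

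If 24–50 is judged on completers, which is the natural reading for a 12-month SD, any refusal at 20% prevalence takes the expected number below 24, while at 25% up to 20% can refuse. Whether the range is missed in practice cannot be settled from the article. The importance is moderate: no analysis depends on the 40, but it is the figure set against the only sample-size rationale given.

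**What to change.** Rewrite the chain in the Sample size section as a range: 160 × 20–25% × a stated Part B consent assumption × 75% retention. Give the basis for the consent assumption. As an illustration only, 70% consent would read as about 22–28 randomised and 17–21 completing.

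In the same paragraph:

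- count those who decline Part B in the observation arm and revise the 120 and 90 to match;
- state whether the 25% loss runs from enrolment or from randomisation, and how much is expected before the 2-month screen;
- state whether 24–50 refers to participants randomised or completing.

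The cost is one reworded paragraph and less favourable anticipated figures. No extra patients and no change to design or analysis are needed.
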